### Compliance

The patient’s compliance will be calculated as “actual dose/dose to be taken”; if the compliance is in the range of 0.7 to 1.2, it will be regarded as good compliance. Participants should return unused medicine and empty packaging at each visit, and TCM physicians will count the number of drugs and granules returned and keep a record of lost and unreturned medicines.

### Auditing

The clinical trial contract is drafted according to the contract template provided by the Good Clinical Practice institution, with the purpose of effectively protecting the safety of the subjects, and we shall be responsible for reporting the results of data safety monitoring to HRPPs on a regular basis. After the trial is completed, if there is a situation where the trial results directly affect the safety of the subjects, we have the responsibility to inform the investigator and the research institution, etc., of the results of the trial in a timely manner. The contract is initially reviewed and costed for the trial project by an institutional office independent of the drafter and signatory, and then reviewed. The clinical trial contract is signed under the premise of fairness, impartiality and openness.

### Ethics and dissemination

#### Patient consent

The trial is approved by the Ethical Review Committee of Xiyuan Hospital of China Academy of Chinese Medical Sciences. For eligible participants, a TCM physician will provide written informed consent forms. After the physician communicates the details of the study, participants willing to participate in the trial will sign an informed consent form. Participates and the TCM physician will each keep a copy of the form.

#### Confidentiality

All materials related to the trial will be safely stored in the restricted access location. All participant case reports and electronic charts will be kept confidential, and only authorized researchers will be able to access the paper version and electronic data set.

#### Protocol amendments

The trial protocol may be modified if we deem it necessary as new information becomes available during the trial or if we need to or management requests it. Once a modification is made to the trial protocol, re-approval from the Ethical Review Committee is required. If for ethical reasons (e.g., low efficacy, serious adverse events) or if the certainty of the trial becomes unacceptable, we will terminate the trial early.

### Outcomes and analysis

Participants in both the intervention group and control group will be encouraged to complete the treatment in 6 weeks, and follow-up will continue for 4 weeks. The following outcome indicators will be used to evaluate efficacy and safety. Demographic and clinical details of participants will be collected at the beginning of the trial. Physical safety examinations will be conducted at the beginning and end of the study, including (1) routine tests of blood, urine and stool, and fecal occult blood; (2) liver function tests (ALT, AST) and kidney function tests (Cr, BUN); and (3) electrocardiograms. Outcome indicators for efficacy evaluation will include the following: (1) a visual analog scale (VAS) for heartburn and regurgitation, (2) a major symptoms scale, (3) PPI withdrawal rate and symptoms recurrence rate, (4) a minor symptoms scale, (5) the MOS 36-item Short From Health Survey (SF-36), (6) the Patient-Reported Outcome (PRO) scale for chronic gastrointestinal diseases, (7) Self-Rating Anxiety Scale (SAS), (8) Self-Rating Depression Scale (SDS), (9) the Gastroesophageal Reflux Disease-Health-Related Quality-Of-Life (GERD-HRQL) scale, and (10) the TCM syndromes scale. Scales and questionnaires will be completed at the beginning and end of the trial and at the end of each phase and follow-up. Adverse events will be observed throughout the treatment.

### Primary outcomes

The primary outcomes are the VAS for heartburn and regurgitation and the major symptoms scale.The VAS is a line marked with 10 scales, with 0 points to 10 points at both ends. Zero points indicates no symptoms, and 10 points represents the most severe and unbearable symptoms. 0–2 is classified as “basic no symptoms,” 3–5 is classified as “mild,” 6–8 is classified as “moderate,” and 8–10 is classified as “severe” [27–29]. Patients will be given a VAS for regurgitation and heartburn daily through a diary card, and the average score of the two symptoms each week will be evaluated according to the content of the diary card. Participants were defined as responders if for at least 50% of weeks during the 6 weeks of the trial the weekly VAS score was reduced from baseline by ≥ 50%. We will calculate the percentage of responders. At the same time, the change in VAS score will be compared between groups.Major symptoms scale: For the main clinical symptoms of NERD, heartburn frequency, heartburn relief time, and regurgitation frequency, the scoring criteria are shown in Table 2.

**Table 2 Tab2:** Major symptoms scale

	Score		
	Mild (0)	Moderate (1)	Severe (2)
Symptom			
Heartburn frequency	1 day a week	2–3 days a week	4–7 days a week
Heartburn relief time	Relieve within 1h	Relieve within 1-3h	> 3 h does not relieve even all day
Regurgitation frequency	1 day a week	2–3 days a week	4–7 days a week

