### Secondary outcomes

Secondary outcomes are the PPI withdrawal rate and symptoms recurrence rate, scales about minor symptoms, health-related quality of life, mental health, and TCM syndromes.PPI withdrawal rate and symptoms recurrence rate: During patient follow-up for the 4 weeks after the end of the treatment, according to the above scores, the number of recurrences and corresponding recurrence rates. The PPI withdrawal rate will calculated based on the number of people who no longer use PPIs at follow-up.Minor symptoms scale: Scoring the frequency and degree of clinical minor symptoms. For the frequency, 0 points indicates no symptoms, 1 points indicates < 1 day per week, 2 points indicates 1 day per week, 3 points indicates 2–3 days per week, 4 points indicates 4–5 days per week, and 5 points indicates 6–7 days per week. For the degree of symptoms, 1 points means no symptoms; 2 points means symptoms are mild; 3 points means symptoms are moderate, need to take medicine occasionally; 4 points means symptoms are severe, need to take medicine for long time; and 5 points means symptoms are very serious, and affecting daily life, need to take medicine for long time. Details are shown in Table 3.SF-36: As a concise health questionnaire, the SF-36 comprehensively evaluates the quality of life of the respondents from 8 dimensions including Physical Functioning (PF), Role-Physical (RP), Bodily Pain (BP), General Health (GH), Vitality (VT), Social Functioning (SF), Role-Emotiona (RE), and Mental Health (MH). It also contains another health dimension: Health Transition (HT), which is used to evaluate the overall change in health in the past year [30–33].PRO: This scale is for patients with FGIDs. It contains a total of 35 items, divided into 6 dimensions (regurgitation, dyspepsia, general condition, social function, defecation, psychology) to assess the influencing factors of chronic gastrointestinal diseases. Each item is graded on a 5-point scale, with a maximum of 4 points and a minimum of 0 points. The higher the score, the more severe the symptoms [34, 35].SAS: The SAS scale is a 20-item self-reported assessment device. Each question is scored on a Likert-type scale of 1 to 4 (based on the following replies: “a little of the time,” “some of the time,” “a good part of the time,” and “most of the time”). The total score is obtained by summing the assessment of the 20 items. The total score multiplied by 1.25 gives the standard score. A standard cutoff score of 50 is usually used to diagnose anxiety. The standard score ranges are 25–49 (normal range), 50–59 (mild anxiety), 60–69 (moderate anxiety), and 70 (severe anxiety) [36, 37].SDS: The Self-Rating Depression Scale (SDS) developed by Zung is a norm-referenced measure, used to screen adults for the potential presence of depressive disorders. The scale produces raw scores between 20 and 80; Zung recommended converting these to Index Scores (which ranged between 25 and 100) by the simple process of multiplying by 1.25. Zung’s recommended cut-off for identifying adults with depressive disorder was index scores of 50 and over [38]. We used in this study an index score of 53 (raw score 42); this was more appropriate for use with Chinese populations [39].GERD–HRQL: A total of 16 items are used to evaluate the symptoms of heartburn, regurgitation, and the effects of current medication on life. Each item is scored on a 6-point scale, from 0 to 5 points. A score of 0 indicates no symptoms, and a score of 5 indicates that symptoms are incapacitating when performing daily activities [40, 41].TCM syndromes scale: a 15-item scale based on *the Clinical Guideline of New Drugs for Traditional Chinese Medicine*. This scale evaluates the changes in TCM symptoms of the digestive tract and the whole body of the participants, including flatulence, stomachache, poor appetite, heartburn, belching, acid reflux, pharyngeal paraesthesia, thirst, distention in the lateral lower abdomen, fatigue, shortness of breath, unwillingness to speak, somatosensory heaviness, fear of cold, and loose stool. Each item is scored, with 1 being asymptomatic and 4 being severe. The higher the overall score, the more severe the overall symptoms [42].

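### The scoring table of the major symptoms scale, a primary outcome, has no level for a symptom-free week, so complete relief cannot be identified on that scale

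*Protocol article*

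**What the plan says.** Under Primary outcomes, the protocol article states: "The primary outcomes are the VAS for heartburn and regurgitation and the major symptoms scale". The second of these has three items, and the only scoring rule given is a pointer to a table: "heartburn frequency, heartburn relief time, and regurgitation frequency, the scoring criteria are shown in Table 2".

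Table 2 has three levels, Mild (0), Moderate (1) and Severe (2). For both frequency items, 0 is one day a week, 1 is 2–3 days and 2 is 4–7 days. For relief time, 0 is "Relieve within 1h", 1 is relief within 1–3 h and 2 is longer than 3 h. No text says how a week without symptoms is scored.

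Other scales in the article do provide for absence of symptoms. For the VAS: "Zero points indicates no symptoms, and 10 points represents the most severe and unbearable symptoms". For the frequency part of the minor symptoms scale: "0 points indicates no symptoms, 1 points indicates < 1 day per week, 2 points indicates 1 day per week". As described under Secondary outcomes, the GERD-HRQL (0) and the TCM syndromes scale (1) also have a level for no symptoms.

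Two further passages bear on the point. Statistical analysis says that missing outcomes are handled by carrying the last record forward or by multiple imputation. Secondary outcomes says recurrence is counted "according to the above scores, the number of recurrences and corresponding recurrence rates".

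**The concern.** Freedom from symptoms is the best result a participant can reach, and this primary outcome has no score for it. The relief-time item is the plainest case: a participant who had no heartburn that week cannot answer it truthfully. With no rule, a site can enter the lowest score or leave the item blank. The six centres may choose differently, at any of the nine time points at which Table 1 schedules the scale.

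At stake is the scale's ability to show a difference between the arms at its lower end. If more participants become symptom-free in one arm than in the other, that difference is compressed when 0 is entered. When the item is left blank, it is replaced by values that describe symptoms. Because recurrence is counted from scores listed earlier in the article, a secondary outcome may inherit the ambiguity.

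**Working it through.** No stated figure needs to be reproduced. The sample size rests on effective rates of 90% and 70% and does not use this scale. The check is a mapping of every possible number of symptomatic days per week to the scores in the article.

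**Step 1: is the table complete as shown?** The header has three labels and every row has three filled cells. A column lost in text extraction is unlikely.

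**Step 2: map days per week to scores.**

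| Symptomatic days per week | Table 2 frequency item | Minor symptoms frequency score |
|---|---|---|
| 0 | no level | 0 |
| 1 | 0 | 2 |
| 2–3 | 1 | 3 |
| 4–5 | 2 | 4 |
| 6–7 | 2 | 5 |

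On the minor symptoms scale, a symptom-free week and a week with one symptomatic day are two points apart (2 − 0 = 2). In Table 2 the first has no score and the second has the minimum.

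**Step 3: floor reading (a symptom-free week is entered as 0).** Improvement on one frequency item:

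- 1 day to 0 days: 0 − 0 = 0 points
- 2–3 days to 1 day: 1 − 0 = 1 point
- 2–3 days to 0 days: 1 − 0 = 1 point

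The first change is not seen, and the second and third cannot be told apart. The article defines no total. If the three items were summed (an assumption), the range would be 0 to 3 × 2 = 6. The minimum of 0 would already belong to a participant with heartburn one day a week, relieved within an hour, and regurgitation one day a week.

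**Step 4: blank reading (a symptom-free week is not scored).** The item is then a missing outcome under Statistical analysis. Carry-forward inserts the participant's last recorded level. Multiple imputation draws on recorded levels. Every recordable level describes at least one symptomatic day, or a heartburn episode, so neither method can return absence. The value is missing because the participant had complete relief.

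**Step 5: after adding a level for none.** With 0 days = 0, 1 day = 1, 2–3 days = 2 and 4–7 days = 3, the same three changes score 1 − 0 = 1, 2 − 1 = 1 and 2 − 0 = 2. All improvements register, and complete relief is distinct.

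**The case against.** The strongest reply is that the trial can still see complete relief. The VAS is also primary, is anchored at no symptoms, and is recorded every day: "Patients will be given a VAS for regurgitation and heartburn daily through a diary card". The only responder definition uses the VAS, and the sample size rests on a proportion, which Table 2 does not yield. A reader might infer that the best result of treatment is invisible to the trial. The documents do not support that, since it is lost on one of two primary measures.

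Three other inferences also go too far:

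- **That the best responders are removed.** The analysis is intention-to-treat with carry-forward or multiple imputation, so a blank would be filled, possibly with a wrong value, and the participant would stay in. That sites would leave blanks is itself conjecture; entering the lowest score is at least as plausible.
- **That the gap favours the granules.** Compression at the floor costs sensitivity and does not by itself favour the active arm. Movement from 4–7 days to 2–3 days or to 1 day still registers.
- **That a primary scale must have as many levels as a secondary one.** Nothing requires this. The comparison with the minor symptoms scale matters only because that scale has a level for none.

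It is also fair to say that the number of participants who would reach zero days is unknown. They enter with an unsatisfactory response to more than 8 weeks of PPI, and their acid suppression is then withdrawn in steps.

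These replies lower the severity. They do not remove the gap. Nor is it a detail that a condensed article left out: the scoring table is printed in full and omits the most favourable state.

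**Conclusion.** The point holds in a limited form. Table 2 gives no valid score for a symptom-free week on any of the three items of a primary outcome, and both likely workarounds misstate such a week. The article supports a size only per item and only on the floor reading: no points for 1 to 0 days, and the same single point for 2–3 days to 0 as for 2–3 days to 1. The effect on the comparison between arms cannot be estimated, because the article gives no distribution of symptomatic days. The effect on recurrence is possible but not certain, because the article does not say which of its scores define a recurrence, or at what threshold.

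This should be fixed. It does not threaten the trial as a whole, because the VAS registers absence of symptoms.

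**What to change.** Before unblinding, add an explicit level for none to all three items of Table 2 and move every other level up by one:

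| Item | 0 | 1 | 2 | 3 |
|---|---|---|---|---|
| Heartburn and regurgitation frequency | 0 days | 1 day | 2–3 days | 4–7 days |
| Heartburn relief time | no heartburn that week | within 1 h | 1–3 h | > 3 h |

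The shift on the relief-time item is essential. Setting no heartburn to 0 while leaving relief within an hour at 0 would recreate the same merge.

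For weeks already recorded, identify symptom-free weeks from the daily heartburn and regurgitation VAS diary, using one prespecified cut-off for a symptomatic day. VAS > 0 is a natural choice. VAS > 2 can serve as a sensitivity analysis, because the article places 0–2 in its band for essentially no symptoms, and the two cut-offs can give different day counts. The rule should also say which source prevails if diary and scale disagree. This assumes that the daily scores are kept separately for each symptom and cover the follow-up weeks at which the scale is scored; the article does not state either.

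The cost is a scoring amendment, which needs ethics re-approval under Protocol amendments, and a scale that no longer matches Table 2 as printed. No new visit or form is needed. Moving the scale to the secondary outcomes would be a larger change than the defect warrants.

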### Secondary outcomes

Secondary outcomes are the PPI withdrawal rate and symptoms recurrence rate, scales about minor symptoms, health-related quality of life, mental health, and TCM syndromes.PPI withdrawal rate and symptoms recurrence rate: During patient follow-up for the 4 weeks after the end of the treatment, according to the above scores, the number of recurrences and corresponding recurrence rates. The PPI withdrawal rate will calculated based on the number of people who no longer use PPIs at follow-up.Minor symptoms scale: Scoring the frequency and degree of clinical minor symptoms. For the frequency, 0 points indicates no symptoms, 1 points indicates < 1 day per week, 2 points indicates 1 day per week, 3 points indicates 2–3 days per week, 4 points indicates 4–5 days per week, and 5 points indicates 6–7 days per week. For the degree of symptoms, 1 points means no symptoms; 2 points means symptoms are mild; 3 points means symptoms are moderate, need to take medicine occasionally; 4 points means symptoms are severe, need to take medicine for long time; and 5 points means symptoms are very serious, and affecting daily life, need to take medicine for long time. Details are shown in Table 3.SF-36: As a concise health questionnaire, the SF-36 comprehensively evaluates the quality of life of the respondents from 8 dimensions including Physical Functioning (PF), Role-Physical (RP), Bodily Pain (BP), General Health (GH), Vitality (VT), Social Functioning (SF), Role-Emotiona (RE), and Mental Health (MH). It also contains another health dimension: Health Transition (HT), which is used to evaluate the overall change in health in the past year [30–33].PRO: This scale is for patients with FGIDs. It contains a total of 35 items, divided into 6 dimensions (regurgitation, dyspepsia, general condition, social function, defecation, psychology) to assess the influencing factors of chronic gastrointestinal diseases. Each item is graded on a 5-point scale, with a maximum of 4 points and a minimum of 0 points. The higher the score, the more severe the symptoms [34, 35].SAS: The SAS scale is a 20-item self-reported assessment device. Each question is scored on a Likert-type scale of 1 to 4 (based on the following replies: “a little of the time,” “some of the time,” “a good part of the time,” and “most of the time”). The total score is obtained by summing the assessment of the 20 items. The total score multiplied by 1.25 gives the standard score. A standard cutoff score of 50 is usually used to diagnose anxiety. The standard score ranges are 25–49 (normal range), 50–59 (mild anxiety), 60–69 (moderate anxiety), and 70 (severe anxiety) [36, 37].SDS: The Self-Rating Depression Scale (SDS) developed by Zung is a norm-referenced measure, used to screen adults for the potential presence of depressive disorders. The scale produces raw scores between 20 and 80; Zung recommended converting these to Index Scores (which ranged between 25 and 100) by the simple process of multiplying by 1.25. Zung’s recommended cut-off for identifying adults with depressive disorder was index scores of 50 and over [38]. We used in this study an index score of 53 (raw score 42); this was more appropriate for use with Chinese populations [39].GERD–HRQL: A total of 16 items are used to evaluate the symptoms of heartburn, regurgitation, and the effects of current medication on life. Each item is scored on a 6-point scale, from 0 to 5 points. A score of 0 indicates no symptoms, and a score of 5 indicates that symptoms are incapacitating when performing daily activities [40, 41].TCM syndromes scale: a 15-item scale based on *the Clinical Guideline of New Drugs for Traditional Chinese Medicine*. This scale evaluates the changes in TCM symptoms of the digestive tract and the whole body of the participants, including flatulence, stomachache, poor appetite, heartburn, belching, acid reflux, pharyngeal paraesthesia, thirst, distention in the lateral lower abdomen, fatigue, shortness of breath, unwillingness to speak, somatosensory heaviness, fear of cold, and loose stool. Each item is scored, with 1 being asymptomatic and 4 being severe. The higher the overall score, the more severe the overall symptoms [42].

**Table 3 Tab3:** Minor symptoms scale

Symptoms	Frequency score	Degree score
Non-cardiogenic chest pain		
Epigastric pain		
Epigastric discomfort		
Belch		
Cough		
Asthma		
Pharyngeal paraesthesia		
Total		

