**Discussion:**

Previous research has shown that TCM is capable to alleviate NERD symptoms. This trial will help to provide a better understanding of the synergistic efficiency of the combination of TCM and PPIs, to explore whether the dosage of PPIs can be reduced after the supplement of TCM granules and to provide a feasible plan to reduce dependencies or withdraw NERD patients from PPIs. The outcome of this trial is expected to reduce the symptom recurrence rates, lessen patients’ physical and psychological burdens, and achieve good social benefits.

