### Cointerventions

One week prior to the start of treatment, patients will be required to stop their intake of other drugs related to TCM therapies of NERD; however, acid-suppressive drugs intake will remain unchanged. During the study period, patients will be forbidden to add any drugs other than study therapies without permission. During the 1–4 weeks of the treatment period, if the participant’s symptoms increase after the reduction of PPIs according to the study protocol and cannot be tolerated, participant can temporarily use almagate suspension or almagate chewable tablets and record the combined medication. During the treatment period of 5–6 weeks, if the participant is unable to tolerate the symptoms after stopping the acid suppressive drugs, participant will be terminated from the trial and recorded and will be treated with their original treatment therapy.

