### Timeline

The entire trial period will last 10 weeks (the treatment period is 6 weeks and the follow-up period will last 4 weeks). Participants will need to stop using drugs related to the treatment of NERD during pre-screening and screening, complete a physical safety examination, and sign an informed consent form. At baseline, participants will need to complete the first assessment and then randomly divided into an intervention group and a control group. During the treatment phase, TCM physicians will instruct the participants on how to take the therapy and then evaluate compliance and outcome indicators after 2, 4, and 6 weeks of treatment. The follow-up period will last 4 weeks after the end of treatment. Details are shown in Table 1.

**Table 1 Tab1:** Timeline of the trial

Study period										
	Screening	Baseline	Treatment						Follow-up	
Outcomes	Week -1	Week 0	Week 1	Week 2	Week 3	Week 4	Week 5	Week 6	Week 8	Week 10

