**Assessment**										
VAS of heartburn and reflux		○	○	○	○	○	○	○	○	○
Major symptoms scale		○	○	○	○	○	○	○	○	○
Minor symptoms scale		○	○	○	○	○	○	○	○	○
TCM syndromes scale		○		○		○		○	○	○
SF-36		○		○		○		○	○	○
PRO for chronic gastrointestinal diseases		○		○		○		○	○	○
SAS		○		○		○		○	○	○
SDS		○		○		○		○	○	○
GERD-HRQL		○		○		○		○	○	○
Compliance			○	○	○	○	○	○		
Cointerventions			○	○	○	○	○	○		
Adverse events			○	○	○	○	○	○		

*VAS* visual analog scale, *TCM* traditional Chinese medicine, *SF-36* the MOS 36-item Short From Health Survey, *PRO* Patient-Reported Outcome, *SAS* Self-Rating Anxiety Scale, *SDS* Self-Rating Depression Scale, *GERD-HRQL* the Gastroesophageal Reflux Disease-Health-Related Quality-Of-Life

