### Statistical analysis

This trial will use intention-to-treat (ITT) analysis as the main method to evaluate the outcome results. To deal with missing outcome variables that remain to be recorded, the last record data will be carried over to the end or a multiple imputation method will be used.

Statistical analysis will be conducted using the SPSS 21.0 software. The significance level is established at 0.05, and the limits of the confidence interval are 95%. Descriptive analysis and categorical variables will be described in frequency tables and as percentages or composition ratios; continuous variables will be described in terms of means and standard deviations (SDs), or medians, lower quartiles (P25), upper quartiles (P75), minimum values, and maximum values. Comparative analyses between two groups will be performed for categorical variables using the chi-squared test, Fisher’s exact probability method, the Wilcoxon rank-sum test, or the CMH test. Continuous variables that conform to a normal distribution will be compares using a *t*-test (for homogeneity of variance between groups, with 0.05 as the test level; if the variance is heterogeneous, the Welch-Satterthwaite *t*-test will be used), while those that conform to a non-normal distribution will be compared using the Wilcoxon rank-sum test or the Wilcoxon signed-rank test. Hypothesis testing will use the two-sided test uniformly, and *P* ≤ 0.05 will be considered statistically significant.

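### The PPI withdrawal rate has no denominator and no rule for participants terminated in weeks 5-6, and Table 1 schedules no medication record at the follow-up visits on which it rests

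*Protocol article*

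**What the plan says.** - **Outcome.** Under Secondary outcomes: "Secondary outcomes are the PPI withdrawal rate and symptoms recurrence rate". The withdrawal rate is specified in one sentence: "The PPI withdrawal rate will calculated based on the number of people who no longer use PPIs at follow-up". The recurrence rate is likewise counted over the 4 weeks of follow-up, with no denominator.
- **Step-down.** Under Intervention group, PPIs are halved in weeks 1-2 and replaced by famotidine in weeks 3-4, and all acid suppression stops in weeks 5-6. The Control group section applies the same step-down.
- **Failures.** Under Cointerventions, for someone who cannot tolerate symptoms in weeks 5-6: "participant will be terminated from the trial and recorded and will be treated with their original treatment therapy".
- **Schedule.** Under Timeline: "The follow-up period will last 4 weeks after the end of treatment". Table 1 has follow-up columns at weeks 8 and 10. The symptom, quality-of-life and mental health scales are marked there. The "Cointerventions" row, like Compliance and Adverse events, is marked only for weeks 1-6.
- **Analysis.** Under Statistical analysis: "This trial will use intention-to-treat (ITT) analysis as the main method to evaluate the outcome results". For missing outcomes, "the last record data will be carried over to the end or a multiple imputation method will be used". Dropout criteria also allows a dropout's last main efficacy measure to be used as the final result.
- **Purpose.** The abstract's discussion says the trial is meant "to provide a feasible plan to reduce dependencies or withdraw NERD patients from PPIs".

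**The concern.** Being off PPIs from week 3 is the assigned regimen, not a result. What tells a successful withdrawal from a failed one is what happens after that. Part of it happens in weeks 5-6, when those who cannot manage leave and resume their original therapy. The rest happens during follow-up, when others may restart a PPI.

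The outcome definition does not cover the first group, and the visit schedule does not visibly capture the second. If the arms differ in terminations, as they would if the granules work, the choice of denominator and of status for the terminated participants affects the size of the reported difference and can change its direction. The definition leaves both choices open until the data are known, for an outcome tied to one of the trial's stated purposes.

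**Working it through.** **1. Reading the sections together.** Take a participant terminated in week 5.
- By the step-down schedule, the last scheduled in-trial status is off PPI.
- By the Cointerventions section, the actual status afterwards is back on original therapy. Inclusion requires more than 8 weeks of PPI treatment, so this is a withdrawal failure.
- The outcome sentence looks at follow-up, when this person is no longer in the trial.
- The missing-data rule offers carry-forward, which could assign off PPI, or multiple imputation, which would impute a status already known.

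Three treatments of this person fit the text: excluded, counted as not withdrawn, or counted as withdrawn.

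**2. Inputs.** The plan states no expected withdrawal or termination rate, so there is no figure of its own to reproduce, and the sample size does not depend on this point. From Sample size estimation: N = 87 per arm. Assumed: terminations t = 9 (intervention, 9/87 = 10.3%) and 17 (control, 17/87 = 19.5%), and a share q = 0.80 off PPIs among those followed, the same in both arms.

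**3. Formulas.**
- Followed only: rate = q
- All randomised, terminated = not withdrawn: rate = q(N - t)/N
- All randomised, off-PPI status carried forward: rate = [q(N - t) + t]/N

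**4. Results.** The numbers followed are 87 - 9 = 78 and 87 - 17 = 70.

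| Rule | Intervention | Control | Difference (points) |
|---|---|---|---|
| Followed only | 80% | 80% | 0 |
| Terminated = not withdrawn | 0.8 x 78/87 = 71.7% | 0.8 x 70/87 = 64.4% | +7.4 |
| Carried forward | (62.4 + 9)/87 = 82.1% | (56 + 17)/87 = 83.9% | -1.8 |

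With equal q, the second difference is q(tC - tI)/N = 0.8 x 8/87 = +7.4 points. The third is -(1 - q)(tC - tI)/N = -0.2 x 8/87 = -1.8 points. Whenever terminations differ and q lies between 0 and 1, these two have opposite signs.

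**5. Range over the assumptions.** The followed-only difference is 0 in every row, because q is set equal in both arms.

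| Terminated (intervention vs control) | q | Terminated = not withdrawn | Carried forward |
|---|---|---|---|
| 9 vs 17 | 0.70 | 62.8% vs 56.3% | 73.1% vs 75.9% |
| 9 vs 17 | 0.90 | 80.7% vs 72.4% | 91.0% vs 92.0% |
| 5 vs 15 | 0.80 | 75.4% vs 66.2% | 81.1% vs 83.4% |
| 10 vs 30 | 0.80 | 70.8% vs 52.4% | 82.3% vs 86.9% |
| 17 vs 17 | 0.80 | 64.4% vs 64.4% | 83.9% vs 83.9% |

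**6. Schedule check.** Nine rows of Table 1, from the VAS to GERD-HRQL, are marked at weeks 8 and 10. None of them records drug use. GERD-HRQL is described as covering the effect of current medication on life, not whether a PPI was taken.

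**The case against.** A reader might infer that the plan counts only those still followed. The text does not say so. It fixes a numerator and leaves the denominator open, and ITT is named as the main method. On an ITT reading the count could be placed over all randomised participants, and someone back on original therapy would then simply not be in the numerator. That stands: followed-only is one possible reading, not the stated rule.

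A reader might also infer that the question of PPI withdrawal cannot be answered. That goes too far. The outcome is secondary, terminations in weeks 5-6 are recorded, and they can be counted as failures without new data. Because they are recorded, the last record may be the failure itself, so carry-forward could misclassify these participants but need not.

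On Table 1, the Cointerventions row concerns added medication during treatment, and there is no row for the withdrawal or recurrence rate at all. The outcome sentence implies that PPI use is established at follow-up, and the case report form, not shown, may collect it. What remains is that the published schedule marks no such record at the visits that define the outcome.

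The sizes are wholly assumed, and with equal terminations the arms do not differ under any rule. That also stands.

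Naming ITT does not settle the matter, however. It says who is analysed, not what status a terminated participant receives, and the missing-data options offered alongside it do not assign the status that is already known.

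**Conclusion.** The concern holds as a defect in the definition and scheduling of a secondary outcome. The protocol gives the PPI withdrawal rate no denominator, assigns no status to participants terminated in weeks 5-6 and returned to original therapy, and marks no medication record at weeks 8 and 10. This goes beyond detail that an article may leave out, because the outcome definition, the termination rule and the visit schedule are all stated and do not fit together.

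Under the assumed 9 versus 17 terminations and 80% off PPIs among those followed, the between-arm difference is 0, about +7 or about -2 points, depending on the rule chosen. Size and sign rest on differential termination, which the documents do not give, so no direction of bias can be asserted for this trial.

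The recurrence rate shares the missing denominator. A reader might infer that it too is restricted to a selected group. The text does not state that, and assessing recurrence among those who improved could be legitimate if it were stated.

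**What to change.** - Define the PPI withdrawal rate over all randomised participants.
- Count anyone terminated in weeks 5-6 and returned to original therapy as not withdrawn, and do not carry forward their last in-trial status. Participants lost for other reasons have a genuinely missing status, which is a matter for the missing-data method.
- Add a record of PPI and other acid-suppressant use at weeks 8 and 10, by marking the Cointerventions row of Table 1 at those visits.
- State the denominator of the recurrence rate. The endpoint itself need not be replaced.

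The cost is endpoint wording and one question at two visits that already take place. The reported rate may look slightly less favourable than under the other readings. Treatment, rescue and termination rules are unaffected.
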